### 2.8. Safety Assessment

All adverse events and reactions will be recorded in detail, including the variety, occurrence time, incidence, severity, duration, therapeutic measures, and outcomes. Some examinations should be taken to monitor the adverse events and reactions, including blood routine examination, stool routine examination, liver function test, renal function test, electrocardiograph (ECG), computed tomography (CT), and magnetic resonance imaging (MRI). It should be highlighted and analyzed in particular about the abnormal inspection indicators, cases of study suspension due to adverse events, and the causality between the adverse events and the test drugs.

### 2.9. Data Management and Monitoring

For efficient and convenient statistics, this study will adopt electronic case report form (eCRF) to record data. The data inputter in each center should timely and accurately record data and upload it to the statistical system after requesting and obtaining the sequential number and the random grouping code. After being reviewed by the inspectors and checked by the data administrator, the data will be locked for statistical analysis subsequently.

This clinical trial will introduce a third-party monitoring team to strengthen the research quality control during the whole process. In accordance with the Good Clinical Practice (GCP) requirements issued by the State Food and Drug Administration (SFDA), a dedicated inspector will be assigned to make regular on-site monitoring visits to the clinical centers to ensure strict adherence to the protocol and correct filling of the test data.

### 2.10. Statistical Analysis

This study cooperates with Statistics Department of Nanjing University of Traditional Chinese Medicine. After the test trial is determined, a special statistician will be employed for making the statistical analysis plan. All data will be statistically analyzed by SAS 9.3 software. Enumeration data will be expressed as percentage, while measurement data will be expressed as mean ± standard deviation. For comparison of count or grade data, chi-square test will be used. Two logistic multiple regressions (Enter method) will be used to analyze the factors affecting the objective curative effect.

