### 2.2. Study Design

This study is designed as a randomized, double-blind, placebo-controlled, and multicenter clinical trial that will last for 18 months from January 2021 to June 2022. It will be conducted in 30 clinical centers in China, and each center will have an investigator for enrolling the patients and collecting the data. The centers and their investigators are listed in Table 1.

The trial was registered at ClinicalTrials.gov (ID: NCT04690283), and the protocol version is 1.2/20200506. The flow chart is shown in Figure 1. The schedule of enrollment, interventions, and assessments is shown in Figure 2.

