### 2.5. Randomization, Allocation, and Blinding

Randomization and blinding are controlled from the drug production source. All the test drugs are designed with the same appearance, dose, and smell, and each drug package has a corresponding drug number. Every six drug numbers are formed into a group, randomly corresponding to six test drugs, which necessarily include two mimetic granules of YWF, two HGWD granules, and two DSD granules, so that the whole is in accordance with the ratio of 1:1:1. Each center must recruit subjects in units of six (at least six subjects), and each recruited subject will be randomly assigned a sequential number and a corresponding drug number. Although the sequential and drug numbers are public, the specific properties of the drug are unknown to anyone, including subjects, investigators, and third-party inspectors.

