#### 2.7.1. Primary Outcome

The degree of oxaliplatin-induced peripheral neuropathy will be evaluated according to the score of European Organization for Research and Treatment of Cancer Quality of Life Questionnaire-CIPN twenty-item scale (EORTC QLQ-CIPN20, 20–80 scores, with higher scores meaning a worse outcome), which is evaluated by the subject on 1 day before and 3 consecutive days after the first time of oxaliplatin administration. Subsequent assessments will be made every one time from cycle 2 to cycle 6, 1 month after the end of cycle 6, and then every 3 months up to 1 year.

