#### 2.7.2. Secondary Outcome

The grades of oxaliplatin-induced peripheral neuropathy will be evaluated according to the grades of National Cancer Institute-Common Terminology Criteria for Adverse Events Version 5.0 (NCI-CTCAE 5.0, 0–5 grades, with higher grade meaning a worse outcome), which is evaluated by the doctor on 1 day before the oxaliplatin administration from cycle 1 to cycle 6, 1 month after the end of cycle 6, and then every 3 months up to 1 year.QOL will be evaluated according to the score of European Organization for Research and Treatment of Cancer's Core Quality of Life Questionnaire (EORTC QLQ-C30, 28–112 scores, with higher scores meaning a worse outcome) on 1 day before the oxaliplatin administration from cycle 1 to cycle 6, 1 month after the end of cycle 6, and then every 3 months up to 1 year.Chemotherapeutic efficacy will be evaluated according to Response Evaluation Criteria in Solid Tumors Version 1.1 (RECIST 1.1) at the end of cycle 3 (and cycle 6 if it exists).The number of completed chemotherapy cycles will be recorded at the end of cycle 6 or after the last chemotherapy. If the result is less then 6, the specific reason should be noted.

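### The doctor-graded neuropathy outcome is ordered, but section 2.10 names a chi-square test for grades; on the full grade table this ignores the order and loses power against a general downward shift

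*Protocol article*

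**What the plan says.** - **Test.** Section 2.10 (Statistical Analysis): "For comparison of count or grade data, chi-square test will be used". No trend, rank, ordinal or stratified form is named. The only chi-square test named by type in the article is Pearson's, in section 2.4 (Sample Size Calculation).
- **Outcome.** Section 2.7.2 (Secondary Outcome) lists the NCI-CTCAE 5.0 neuropathy grade, described as "0–5 grades, with higher grade meaning a worse outcome" and rated by the doctor. The primary outcome (section 2.7.1) is a different measure, the patient-reported EORTC QLQ-CIPN20 score.
- **Size.** Section 2.4 assumes an OIPN incidence of 40% on placebo and 20% in each intervention group, 20% dropout, and 120 per group.
- **Allocation.** Section 2.5: "Every six drug numbers are formed into a group, randomly corresponding to six test drugs", two of each kind. Centres recruit in multiples of six, and section 2.2 gives 30 centres. Allocation is therefore in effect blocked within centre.
- **Still to come.** Section 2.10 says that a statistician will write a statistical analysis plan. It mentions logistic regressions without naming covariates.

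**The concern.** The article itself says that a higher grade is worse, then assigns grades to a test that treats them as unordered labels. Pearson's chi-square on a table of k grades by two arms spends k − 1 degrees of freedom on departures in any pattern. If treatment moves patients towards lower grades in general, almost all of the signal lies in one direction, and the extra degrees of freedom only raise the critical value. A real reduction in graded severity could then be missed on this secondary outcome.

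This is not merely a detail left to the later plan. The article has already chosen the test, so that plan must either inherit it or depart from a published method.

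**Working it through.** **Inputs from the article.** 120 per arm less 20% gives 120 × 0.8 = 96 evaluable. Incidences of 40% and 20% give an odds ratio of (0.20/0.80)/(0.40/0.60) = 0.375.

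**Assumptions (not in the article).** Two-sided 5% level; one assessment time; placebo grades 0/1/2/3 = 60/20/14/6%; the same odds ratio at every cut of the scale (proportional odds); odds ratios of 0.375 and, as a smaller effect, 0.5.

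**The plan's own figure.** Alpha and power are not stated, so 120 cannot be confirmed, but nothing shows it to be wrong. For example, a pairwise comparison at 5% and 85% power needs 93, and 93/0.8 = 117. For the yes/no comparison at 96 per arm, the non-centrality is 96 × 0.20²/(2 × 0.30 × 0.70) = 9.14, a power of about 86%.

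**Grades on treatment at odds ratio 0.375.** The placebo probabilities of grade ≥1, ≥2 and ≥3 are 0.40, 0.20 and 0.06. Multiplying their odds by 0.375 gives 0.200, 0.086 and 0.023, so the grades are 80.0/11.4/6.2/2.3%. The average over the two arms, p̄, is 0.700/0.157/0.101/0.042.

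**Pearson on the full table (3 df).** With d the difference between arms in each grade, the non-centrality is λ = n Σ d²/(2p̄):

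96 × (0.0286 + 0.0234 + 0.0298 + 0.0161) = 9.39; critical value 7.81; power 73%.

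**Ordinal row-mean-score (Wilcoxon) test (1 df).** The mid-rank scores are 0.350, 0.779, 0.908 and 0.979. The arm means lie 0.05154 either side of 0.5, and the score variance is 0.05433:

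λ = 96 × 2 × 0.05154²/0.05433 = 9.39; critical value 3.84; power 87%.

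The two tests carry the same signal. Only the degrees of freedom differ.

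| Odds ratio | λ (both tests) | Pearson, 3 df | Ordinal, 1 df | Simulated |
|---|---|---|---|---|
| 0.375 | 9.39 | 73% | 87% | about 74% vs 88% |
| 0.5 | 5.11 | 45% | 62% | about 44% vs 62% |

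**Other assumed placebo mixes, proportional odds, 96 per arm.**

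| Mix (%) | Odds ratio | Arms | Pearson | Ordinal |
|---|---|---|---|---|
| 60/20/12/6/2 | 0.375 | 2 | 68.5% | 86.5% |
| 60/20/12/6/2 | 0.5 | 3 | 42.8% | 66.7% |
| 25/35/25/12/3 | 0.375 | 2 | 84.2% | 95.2% |
| 60/25/10/5 | 0.375 | 2 | 73.0% | 86.4% |

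Over all mixes tried, the gain was about 8 to 24 points. For the first row, 80% power needs 122 evaluable per arm with Pearson and 81 with the ordinal test (122/81 = 1.51).

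**Type I error.** The expected grade 3 count per arm in the main scenario is 96 × 0.042 = 4.0, and some expected cell fell below 5 in 63 to 73% of trials simulated with a treatment effect. Even so, in simulations without an effect Pearson's size was 4.2 to 5.2%, and that of the ordinal test 4.6 to 5.4%.

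**When the shift is not consistent** (same placebo mix, treatment mixes assumed):

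| Treatment mix (%) | Pattern | Pearson | Ordinal |
|---|---|---|---|
| 60/33/5/2 | severe to mild, incidence unchanged | about 72% | about 10% |
| 80/6.7/8.3/5 | benefit mainly at grade 1 | about 80% | about 79% |

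**Centre.** 360/30 = 12 patients per centre on average, 4 per arm. Adding centre strata to the ordinal test gained about 0 points without centre variation and about 4 to 10 points at an assumed centre standard deviation of 1.0 on the log-odds scale. There the unstratified ordinal test was conservative, with a size of about 2 to 3%.

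**The case against.** The strongest reply is that the only quantified hypothesis is incidence, for which Pearson's test is standard. If grades are collapsed to any neuropathy versus none, chi-square power at 96 per arm is about 86 to 88% under the 60/20/14/6% mix, much the same as the ordinal test. This stands: the loss arises only if the full grade table is tested, and the article does not say whether grades will be collapsed. But the outcome is defined as the grades themselves, and collapsing works this well only while most placebo patients stay at grade 0. With an assumed placebo mix of 10/50/30/10% and an odds ratio of 0.375, power is about 68% for yes/no, 85% for Pearson on all grades and 94% for the ordinal test.

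It also stands that proportional odds is the case that favours a rank test. If treatment only turns severe grades into mild ones, the ranking of the tests reverses sharply. The change is not free.

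A reader might infer more than the documents support:
- *That the p-values are unreliable because of sparse cells.* Pearson's size stayed near 5%, and merging upper grades or an exact test is commonly left to the analysis plan.
- *That omitting centre is an error.* Section 2.10 does not rule out stratification, and such detail is commonly left to the analysis plan. The article gives no centre variance, and the cost is some power, not validity.
- *That the trial's main result is at risk.* The grade is a secondary outcome. The primary CIPN20 score is not a grade and is untouched.

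**Conclusion.** The point holds as one of efficiency on a secondary outcome. The article names a test for ordered grades that does not use their order. Against a general downward shift, the cost at 96 per arm is about 14 points of power at an odds ratio of 0.375 (74% vs 88%) and about 18 points at 0.5 (44% vs 62%), with 8 to 24 points over other assumed mixes.

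This rests on three things: reading the unqualified chi-square as Pearson's, which is a fair inference from section 2.4; testing the full grade table; and a roughly proportional shift. The grade mixes are assumptions, since the article gives only the 40% and 20% incidences. False positives are not increased. The change is worth making before the analysis plan is written.

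**What to change.** In section 2.10, replace the single chi-square rule for grades with the following:

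- Compare NCI-CTCAE grades, each active arm against placebo, with an ordinal test (row-mean-score Cochran-Mantel-Haenszel/Wilcoxon) or a proportional-odds model. Report a common odds ratio with its 95% confidence interval.
- Keep chi-square for yes/no incidence.
- Tabulate the full grade distribution by arm, so that a redistribution without a consistent shift can be seen.
- Where practical, stratify or adjust by centre, pooling small centres, because allocation is blocked within centre. This is a minor addition, worth about nothing if centres do not differ.

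The cost is a sentence or two in section 2.10 and a little programming in the planned software. No new data or patients are needed. The statistical price is the weaker test under a severe-to-mild redistribution with unchanged incidence.

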## 3. Discussion

Oxaliplatin is a standard chemotherapy drug for colorectal cancer, and its toxic and side effects must be taken seriously. OIPN is the most common side effect which significantly affects the curative efficacy of chemotherapy and patients' quality of life and remains a refractory problem despite receiving extensive attention from researchers.

For seeking potential effective therapy, the pathogenesis of OIPN has been studied for a long time. Analysis of recent literature suggested that the alteration of voltage-gated Na^+^ channels, K^+^ channels, Ca^2+^ channels, and transient receptor potential (TRP) channels could be related to acute OIPN [2]. On the other hand, platinum accumulating in dorsal root ganglion so as to cause a series of neuronal damage, including nuclear DNA damage, mitochondrial dysfunction, oxidative stress, and axonopathy, is considered as the main mechanism of chronic OIPN [2, 35]. Regarding platinum accumulation, organic cation transporter 2 (OCT2) has been demonstrated to play an important role in platinum uptake and is expected to be a new target for prevention and treatment of OIPN [36, 37].

A number of agents have been proposed with potential therapeutic or preventive effects to OIPN. However, none of them have got recognition by further studies [1, 23]. Combining the theory of TCM, this study attributes OIPN to “arthromyodynia” [29]. YWF granules are a category of prescription granules with similar effects of tonifying qi and warming meridians, and they have been empirically used to treat arthromyodynia in China. In order to obtain scientific and precise evidence, several animal studies and randomized controlled clinical trials with small sample size have been conducted previously. Results showed that YWF granules can ameliorate OIPN syndrome without affecting the antitumor activity of oxaliplatin [30, 33]. Thus, we have designed the protocol for a randomized, placebo-controlled, double-blind, multicenter trial to enlarge the sample size for further evaluation of the preventive efficacy and safety of YWF granules. This study will provide objective evidence for the clinical application of YWF granules in preventing OIPN.

## Figures and Tables

**Figure 1 fig1:**
[figure not shown]
Study flow chart of enrollment, allocation, intervention, and assessment.

**Figure 2 fig2:**
[figure not shown]
Schedule of enrollment, allocation, intervention, and assessment. *Note*. Subjects will complete the EORTC QLQ-CIPN20 questionnaire for 4 consecutive times during cycle 1 (refer to 2.8). EORTC QLQ-CIPN20: European Organization for Research and Treatment of Cancer Quality of Life Questionnaire-CIPN twenty-item scale; NCI-CTCAE 5.0: National Cancer Institute-Common Terminology Criteria for Adverse Events Version 5.0; EORTC QLQ-C30: European Organization for Research and Treatment of Cancer's Core Quality of Life Questionnaire; RECIST 1.1: Response Evaluation Criteria in Solid Tumors Version 1.1.

**Table 1 tab1:** Clinical centers in China.

No.	Organization name	Location	Investigator
1	Jiangsu Province Hospital on Integration of Chinese and Western Medicine	Nanjing, Jiangsu Province	[name]
2	Sir Run Run Hospital	Nanjing, Jiangsu Province	[name]
3	Yancheng Hospital of Traditional Chinese Medicine	Yancheng, Jiangsu Province	[name]
4	Jiangning District Hospital of Traditional Chinese Medicine	Nanjing, Jiangsu Province	[name]
5	Suzhou Hospital of Traditional Chinese Medicine	Suzhou, Jiangsu Province	[name]
6	Huai'an Hospital of Traditional Chinese Medicine	Huai'an, Jiangsu Province	[name]
7	Zhenjiang Hospital of Chinese Traditional and Western Medicine	Zhenjiang, Jiangsu Province	[name]
8	Changshu No. 1 People's Hospital	Changshu, Jiangsu Province	[name]
9	Affiliated Nanjing Jiangbei People's Hospital of Nantong University	Nanjing, Jiangsu Province	[name]
10	The First People's Hospital of Chuzhou	Chuzhou, Anhui Province	[name]
11	Shanghai Changzheng Hospital	Shanghai	[name]
12	Nantong Tumor Hospital	Nantong, Jiangsu Province	[name]
13	Danyang Hospital of Traditional Chinese Medicine	Danyang, Jiangsu Province	[name]
14	Nanjing Drum Tower Hospital	Nanjing, Jiangsu Province	[name]
15	Jiangsu Cancer Hospital, the Affiliated Cancer Hospital of Nanjing Medical University	Nanjing, Jiangsu Province	[name]
16	Jiangsu Province Hospital, the First Affiliated Hospital of Nanjing Medical University	Nanjing, Jiangsu Province	[name]
17	Fudan University Shanghai Cancer Center	Shanghai	[name]
18	Longhua Hospital Shanghai University of Traditional Chinese Medicine	Shanghai	[name]
19	Changhai Hospital	Shanghai	[name]
20	Shuguang Hospital Affiliated to Shanghai University of Traditional Chinese Medicine	Shanghai	[name]
21	Yangzhou Hospital of Traditional Chinese Medicine	Yangzhou, Jiangsu Province	[name]
22	Zhejiang Provincial Hospital of Chinese Medicine	Hangzhou, Zhejiang Province	[name]
23	Hangzhou Hospital of Traditional Chinese Medicine	Hangzhou, Zhejiang Province	[name]
24	The First Affiliated Hospital of Guangxi University of Chinese Medicine	Nanning, Guangxi Province	[name]
25	Henan Cancer Hospital	Zhengzhou, Henan Province	[name]
26	Affiliated Hospital of Traditional Chinese Medicine of Southwest Medical University	Luzhou, Sichuan Province	[name]
27	Affiliated Hospital of Shanxi University of Traditional Chinese Medicine	Xianyang, Shanxi Province	[name]
28	Hunan Academy of Traditional Chinese Medicine Affiliated Hospital	Changsha, Hunan Province	[name]
29	Hebei General Hospital	Shijiazhuang, Hebei Province	[name]
30	The First Affiliated Hospital of Guizhou University of Chinese Medicine	Guiyang, Guizhou Province	[name]

*Note*. Each center was randomly assigned the center number, and the ranking had nothing to do with the center scale and the number of planned enrollment.

**Table 2 tab2:** Chemotherapy regimen.

Abbreviated name	Components	Dosage	Mode of administration	Treatment course
FOLFOX4	Oxaliplatin	85 mg/m^2^	Intravenous infusion for >2 hours on day 1	Every 2 weeks, at least 3 cycles
	Leucovorin	200 mg/m^2^	Intravenous infusion for >2 hours on days 1 and 2	
	5-Fluorouracil	400 mg/m^2^	Intravenous injection on days 1 and 2	
		600 mg/m^2^	Continuous intravenous infusion for 22 hours on days 1 and 2	

mFOLFOX6	Oxaliplatin	85 mg/m^2^	Intravenous infusion for >2 hours on day 1	Every 2 weeks, at least 3 cycles
	Leucovorin	400 mg/m^2^	Intravenous infusion for >2 hours on day 1	
	5-Fluorouracil	400 mg/m^2^	Intravenous injection on day 1	
		1200 mg/m^2^	Continuous intravenous infusion for 22 hours on days 1 and 2	

XELOX	Oxaliplatin	130 mg/m^2^	Intravenous infusion for >2 hours on day 1	Every 3 weeks, at least 4 cycles
	Capecitabine	1000 mg/m^2^	Oral administration twice a day on days 1–14	

**Table 3 tab3:** Standard formulation of YWF granules.

Huangqi Guizhi Wuwu decocion (HGWD) granules			
Pinyin name	English name	Latin name	Doses, g
Huangqi	*Astragalus membranaceus*	Astragali Radix Membranacei	18
Guizhi	Cassia twig	Ramulus Cinnamomi	9
Baishao	Radix Paeoniae Alba	Paeoniae Radix Alba	9
Shengjiang	Ginger	Rhizoma Zingiberis Recens	9
Dazao	Jujube	Fructus Zizyphi Jujubae	9

Danggui Sini decoction (DSD) granules			
Danggui	*Angelica sinensis*	*Angelicae sinensis*	12
Guizhi	Cassia twig	Ramulus Cinnamomi	9
Baishao	Radix Paeoniae alba	Paeoniae Radix Alba	9
Xixin	*Asarum*	Herba Asari Cum Radice	3
Tongcao	Tetrapanax papyrifer	Medulla Tetrapanacis Papyriferi	6
Zhigancao	Honey-fried licorice root	Radix Glycyrrhizae Preparata	5
Dazao	Jujube	Fructus Zizyphi Jujubae	9

## Data Availability

The data and materials are available upon request from the corresponding author.
